#### Molecular platform

Blood samples for biomarker analyses are collected at baseline and at the completion of each treatment phase (Fig. 1). Across sites, SOPs for sample preparation, transfer, receipt, and analysis, as well as material transfer agreements are established. De-identified biological samples are transferred to the Douglas Mental Health University Institute biobank (see [21] for details). In brief, transcriptomics (mRNA and non-coding RNA), DNA methylation and inflammatory cytokines will be examined to identify potential predictive markers of treatment response and changes with ECT and ketamine treatment [21]. Recently published preclinical data have indicated that the 2R,6R-hydroxy-norketamine metabolite of ketamine may be responsible for the rapid antidepressant effects observed with the racemic ketamine mixture [44]. As such, plasma levels of the stereoisomers of ketamine and its metabolites are obtained 2 h after the first infusion (ketamine has a 3 h half-life). This component is an addition to the CAN-BIND molecular platform.

### Data management

As part of the CAN-BIND program, each site has entered into a standardized Participation Agreement with OBI to facilitate transfer of data using multiple bioinformatics approaches [21]. Specific data collection and aggregation platforms are implemented through Centre for Ontario Data Exploration (Brain-CODE, https://www.braincode.ca/) Brain-CODE is a large-scale database and informatics platform developed and maintained by OBI. Brain-CODE is hosted at the Centre for Advanced Computing at Queen’s University in Kingston, Ontario. The centre is a member of the Compute Canada high-performance computing consortium, which supports regulatory-complaint processes for securing the privacy of health care data and provides expansive computing resources for complex data analysis (https://cac.queensu.ca/overview). Data-collection platforms involve REDCap (Research Electronic Data Capture) for clinical and demographic data [45], SPReD (Stroke Patient Recovery Research Database) for neuroimaging data [46], and LabKey [47] for managing molecular workflows, experiments, and raw data.

### Data analyses

The primary outcome measure is the rate of antidepressant response (i.e., percentage of participants meeting antidepressant response criteria [≥ 50% reduction in MADRS scores from baseline and MADRS score < 22]) in each arm at the end of the randomized treatment phase. A total of 240 participants will be enrolled into the randomized treatment phase across the four recruiting sites. This will allow for a 20% drop-out rate (i.e., withdrawal of approximately 40 participants), resulting in a total sample of *N* = 200. For the primary efficacy analyses, a non-inferiority margin of 20% was selected based on clinical judgment. Thus, a sample of 200 participants (*N* = 100/treatment arm) is required to be 90% certain that the upper limit of a one-sided 95% confidence interval will exclude a difference in favour of the ECT group of more than 20%. Secondary efficacy outcomes will include percent change in MADRS scores from baseline to the end of the randomized treatment phase, and remission rates (MADRS score ≤ 10). Response and remission rates will also be assessed for the crossover phase. Clinical scores will be analyzed using linear mixed models (appropriate covariates, such as site, will be included, as needed). Categorical outcomes (response/remission) will be examined using χ^2^ tests. The alpha will be set at 0.05.

Speed of therapeutic effects is defined as the number of treatments required for participants to first meet antidepressant response criteria. A Kaplan-Meier survival analysis will be used to compare the mean number of required treatments for first response to ECT and ketamine during the randomized treatment phase. Side effect burden will be quantified by summing the total frequency and severity scores of the TSES administered after the final treatment during the randomized treatment phase. Mean total TSES scores for ECT and ketamine will be compared using an ANOVA (appropriate covariates will be included). Further, side effect profiles for each treatment will be derived by identifying the most common side effects reported in each arm of the trial (present in > 5% of participants). Treatment tolerability will be estimated via dropout rates. Finally, data from CNS Vital Signs will permit comparison of any cognitive side effects associated with ECT or ketamine (compared at the end of the randomized treatment phase). Level of health care utilization (estimated using average cost of treatment administration, number of days of inpatient hospitalization, and frequency of outpatient consultations) associated with ECT and ketamine will be compared using ANOVAs.

The main outcome in the maintenance phase will be time to relapse. Due to differences in the administration schedules of ECT and ketamine during maintenance, two parallel descriptive statistics will be outlined. For each treatment, mean time to relapse (loss of antidepressant response) will be estimated using Kaplan-Meier survival analysis.

While data from each analytical platform will be analyzed independently using the methods described herein and elsewhere [21], integration of data collected across platforms will also be carried out, and will be overseen by the CAN-BIND Data Science Advisory Team comprised of Principal Investigators, domain-specific informatics advisors, and operations support. In addition to conventional statistical approaches, machine-learning approaches will be applied particularly with regards to outcome prediction (i.e., response/non-response to ECT and ketamine at 3 or 4 weeks of treatment).

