Electroconvulsive therapy (ECT) remains the gold standard in treating severe and/or treatment-resistant MDEs [15]. Response rates to ECT are high (50–80%), and latency to response is shorter than for classical pharmacotherapy [16–18]. Despite these benefits, access to ECT is limited and lengthy wait-lists are common. Moreover, its high costs, potential for side effects, including cognitive deficits, and enduring stigma have resulted in underutilization of ECT as a treatment for MDEs.

One of the current goals in psychiatry is the identification of biological phenotypes (or biomarkers) that could improve characterization of the likelihood that a patient will respond to a specific treatment strategy. This is particularly pertinent in context of ECT or ketamine treatment, as both are currently reserved for the most treatment resistant and severely depressed patients. Candidate biomarkers for outcome prediction in depression include structural and functional neuroimaging profiles, as well as genetic, epigenetic, proteomic, and metabolic features [19]. Currently, it is unclear how baseline biomarker measures moderate clinical outcomes. Exploring how these measures are impacted by ECT or ketamine may further our understanding of the underlying mechanisms of action of these interventions in alleviating depressive symptoms.

The primary objective of this longitudinal, multi-centre non-inferiority trial is to compare acute treatment of MDEs with repeated IV ketamine and ECT in terms of efficacy, speed of therapeutic effects, side effect profiles, and health care resource utilization. A secondary objective is to assess whether ketamine response can be sustained with a gradual spacing of ketamine maintenance infusions, as is the case for ECT. Finally, through the collection of clinical, cognitive, neuroimaging and molecular data according to Canadian Biomarker Integration Network in Depression (CAN-BIND) protocols [20, 21], we aim to identify biomarkers that predict or moderate ketamine or ECT response.

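### The drop-out figures do not agree: 20% of the 240 enrolled is 48, which leaves 192 and not the 200 said to be required

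*Protocol article*

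**What the plan says.** The sample-size text is in the Data analyses section of the protocol article. It fixes enrolment first: "A total of 240 participants will be enrolled into the randomized treatment phase across the four recruiting sites". It then gives the allowance for loss: "This will allow for a 20% drop-out rate (i.e., withdrawal of approximately 40 participants), resulting in a total sample of" 200.

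The same paragraph says that 200 participants, 100 per arm, is the number that "is required to be 90% certain". The criterion is that the "upper limit of a one-sided 95% confidence interval" rules out an advantage for ECT larger than the margin, and "a non-inferiority margin of 20% was selected based on clinical judgment". The endpoint is the response rate at the end of the randomized treatment phase, and allocation is 1:1.

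The sizing text gives no assumed response rate. The only related figure is in the Background, which puts response to ECT at 50–80%.

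**The concern.** Enrolment, drop-out rate, number withdrawn and number remaining are four linked quantities, and fixing two of them determines the others. Here the stated rate and the stated count describe different losses from the same 240 people. A reader who relies on the rate gets a smaller retained sample than the one the article says is needed; a reader who relies on the count gets a lower tolerated drop-out rate than the one stated.

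What is at stake is whether the trial, at its own planned drop-out rate, reaches the sample tied to its 90% figure. A later reader, or a monitoring board comparing actual losses with the plan, would also not know whether 40 or 48 withdrawals is the planned limit.

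**Working it through.** **Inputs from the document:** enrolled 240; drop-out 20%, described as about 40; remaining 200 (100 per arm); one-sided 95% confidence limit, so one-sided alpha 0.05; power 90%; margin 20 percentage points; 1:1 allocation.

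**Assumed here:** the same true response rate p in both arms, varied over the 50–80% range that the Background gives for ECT.

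**Step 1. Can the required 200 be reproduced?** Per arm, n = (1.645 + 1.282)² × 2p(1 − p) / 0.20², rounded up.

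| p | n per arm | total |
|---|---|---|
| 0.50 | 108 | 216 |
| 0.60 | 103 | 206 |
| 0.63 | 100 | 200 |
| 0.65 | 98 | 196 |
| 0.80 | 69 | 138 |

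Solving for n = 100 gives p of about 0.628. So 200 is a sound requirement for a common response rate of about 63%, which lies inside the cited range.

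**Step 2. Can the drop-out allowance be reproduced?**

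- 240 × 0.20 = 48 withdrawals, and 240 − 48 = 192, or 96 per arm.
- 40 / 240 = 16.7%, whereas 40 / 200 = 20%.
- Enrolment that keeps 200 after a 20% loss: 200 / 0.80 = 250.
- 200 × 1.20 = 240, which is the stated enrolment.

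The stated set of figures matches only the last line: the rate was applied to the sample to be retained, not to the sample enrolled. At 20% drop-out the retained sample is 8 below the 200 called for.

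**Step 3. What does the shortfall cost?** Power = Φ(0.20 / √(2p(1 − p)/n) − 1.645). For example, at p = 0.63 and n = 96 the standard error is √(0.4662/96) = 0.0697, and Φ(2.870 − 1.645) = Φ(1.225) = 89.0%.

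| p | power, 100 per arm | power, 96 per arm |
|---|---|---|
| 0.50 | 88.2% | 87.0% |
| 0.63 | 90.0% | 89.0% |
| 0.80 | 97.1% | 96.6% |

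The loss is about 0.5 to 1.2 percentage points. Within the 50–80% range, 100 per arm reaches 90% from a response rate of about 63% upward. With 96 per arm, the condition p(1 − p) ≤ 96 × 0.04 / (2 × 8.564) = 0.2242 gives about 66% upward.

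**The case against.** The best defence is that the error hardly matters. The count is labelled approximate, 200 is itself a reasonable requirement, and about one point of power changes no estimate, test or conclusion. Most of this stands, and it settles the severity. It does not remove the inconsistency: 48 against 40 is a gap of 8 withdrawals, which is more than rounding, and the retained sample is 4% below the stated requirement. It is also a figure that the article states, not a detail left to the full protocol.

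It can also be said that the missing response rate is something a condensed article may leave out. That is fair, and its absence is not raised as a fault. It is only the reason why power has to be shown over a range.

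Three stronger readings are tempting, and the document supports none of them.

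- **That withdrawn patients will be left out of the primary analysis.** The sentence sizes the trial. Nothing in the article says that withdrawn patients are excluded, and no completer or per-protocol analysis is named. Inflating enrolment for drop-out is compatible with analysing everyone randomized, and analysis sets and missing-data handling are commonly left to the full protocol or SAP.
- **That unequal withdrawal will bias the comparison towards non-inferiority.** The article gives no withdrawal rates by arm and no response rate among those who withdraw, so any figure for such bias would come from the reader's own inputs.
- **That analysing all 240 with imputed final ratings would put power back above 90%.** Imputed outcomes do not carry the information of observed ones, so this cannot be promised.

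**Conclusion.** The point holds as an arithmetic inconsistency, and it is minor. Enrolment of 240, drop-out of 20%, about 40 withdrawals and 200 remaining cannot all be true. At the stated rate the trial keeps 192, which falls short of its own requirement by 8; at the stated count the rate is 16.7%.

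The effect on power is at most about 1.2 points over the 50–80% range, and at the response rate that the 200 implies (about 63%) power is 89.0% where 90% is claimed. This rests on equal true response rates in the two arms, the normal approximation, and a response rate that the sizing text does not state. It does not show that the trial is materially underpowered, and it says nothing about who enters the primary analysis.

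**What to change.** Restate the sentence in one of two consistent forms, neither of which needs more patients:

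- enrolling 240 allows for a drop-out rate of about 16.7% (40 participants), leaving 200 (100 per arm); or
- a 20% drop-out rate (48 participants) leaves 192 (96 per arm).

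In either case add the assumed response rate and the power that follows from it: about 90% at 63% response for the first form, about 89% for the second. Keeping both the 20% rate and the 200 would instead mean enrolling 250, which is 10 more patients for about one point of power.

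The cost is one corrected sentence. The design, recruitment and analysis do not change.

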### Treatment schedule

#### Randomized treatment phase

For participants receiving ECT, the number of treatments (9 or 12) is determined by the treating physician. For the ketamine arm, the number of treatments is determined by participants’ antidepressant response as assessed using the MADRS. Participants achieving remission (MADRS ≤10) after 9 ketamine infusions exit the randomized treatment phase and are eligible to enter the maintenance phase (Fig. 1). Participants receiving ketamine who achieve an antidepressant response but not remission after 9 treatments receive an additional 3 infusions (12 treatments total). In both treatment arms, non-responders (< 50% MADRS decrease or a score ≥ 22) after 3 weeks may crossover to receive a full course of treatment with the alternative strategy. Responders after 12 treatments may move on to the maintenance phase.

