### Assessments

#### Clinical platform

Participants in both arms are clinically assessed on an identical schedule. Clinical raters receive standardized training in the administration of measures of interest, and are assessed for inter-rater reliability. They remain blind to treatment arm and are not otherwise involved in the study, while participants are instructed not to disclose their treatment arm during ratings. On visits consisting of both clinical scales and treatment, clinical ratings are administered prior to treatment. Clinical scales are listed in Table 2.

**Table 2 Tab2:** Clinical assessments

*Clinician-Administered Assessments*	
Mini International Neuropsychiatric Interview (MINI)	
Montgomery-Åsberg Depression Rating Scale (MADRS)	
Clinical Global Impression (CGI)	
Young Mania Rating Scale (YMRS)	
Columbia-Suicide Severity Rating Scale (C-SSRS)	
Toronto Side Effects Scale (TSES)	
Montreal Cognitive Assessment (MOCA)	
CNS Vital Signs (CNS-VS), Computerized neurocognitive battery	
*Self-Report Assessments*	
Patient Health Questionnaire (PHQ-9)	
Generalized Anxiety Disorder 7-item scale (GAD-7)	
Quality of Life, Enjoyment and Satisfaction Questionnaire-short form (Q-LESQ-SF)	
Dimensional Anhedonia Rating Scale (DARS)	
Medical Outcome Study - short Form 36 (SF-36)	
Drug Abuse Screening Test (DAST-10)	
Beck Scale for Suicide Ideation (BSS)	

The primary study outcome measure is response rates to randomized treatment determined through percent change in MADRS scores from baseline (pre-randomized treatment phase) to end of randomized treatment. The MADRS is a 10-item scale designed to measure depression severity administered by a blinded rater using the Structured Interview Guide for the Montgomery-Åsberg Depression Rating Scale (SIGMA) [31]. Additional assessments include the Clinical Global Impression, Severity and Improvement Scales (CGI-S and CGI-I) [32], the C-SSRS, and the Young Mania Rating Scale (YMRS) [33]. Clinical assessments are obtained prior to each treatment during the first week (i.e., thrice-weekly), and then at weekly intervals throughout the randomized treatment and crossover phases. When administration of these scales occurs at shorter time intervals than the validated measurement timeframe, symptoms are assessed for the time period since last treatment.

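### Speed of response is to be compared by a Kaplan-Meier mean with no common limit, although observation for a first response ends at 9 treatments for ketamine and can run to 12 for ECT

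*Protocol article*

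**What the plan says.** The Data analyses section of the protocol article fixes the endpoint: "Speed of therapeutic effects is defined as the number of treatments required for participants to first meet antidepressant response criteria". It then fixes the summary: "A Kaplan-Meier survival analysis will be used to compare the mean number of required treatments for first response to ECT and ketamine", within the randomized treatment phase. It names no restriction point and no test.

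The section on the randomized treatment phase determines how long each arm is observed for a first response:

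- ECT: "For participants receiving ECT, the number of treatments (9 or 12) is determined by the treating physician".
- Ketamine: "Participants receiving ketamine who achieve an antidepressant response but not remission after 9 treatments receive an additional 3 infusions". Those in remission after 9 leave the phase.
- Both arms: "In both treatment arms, non-responders (< 50% MADRS decrease or a score ≥ 22) after 3 weeks may crossover to receive a full course" of the other treatment.

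The Background section gives ECT response rates of 50–80% and lists speed of effect within the primary objective. The Discussion says the investigators expect ketamine to act faster.

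**The concern.** A mean time from a Kaplan-Meier curve is the area under the curve, and it is complete only if the curve falls to zero. Here it will not: on the article's own background range 20–50% of ECT patients do not respond, and the design includes a crossover phase for non-responders. What can be estimated is a mean up to a chosen number of treatments, and the article chooses none.

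The choice matters because the stopping rules are not symmetric. A ketamine patient who goes past treatment 9 has already had the event. A ketamine patient without response at 9 has no described route to further ketamine in this phase. For ECT, the choice of 9 or 12 is not tied to response, and crossover after 3 weeks is permitted but not required, so an ECT non-responder can remain under observation to 12. Means taken to different last times are not comparable, and the arm with the longer window gets the larger mean. That direction agrees with what the trial expects to find, so an artefact could be read as confirmation.

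For the maintenance phase, the same section recognises that the schedules differ and limits itself to parallel descriptive summaries. It takes no such care in the acute phase.

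**Working it through.** The article gives no figure for the speed endpoint, so there is none to reproduce. The check asks what the stated summary would show if the two arms had the same response process.

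**Inputs from the article.** Ketamine is observed for first response to treatment 9; ECT to 9 or 12. There are 100 evaluable patients per arm. Ratings follow one schedule in both arms ("Clinical assessments are obtained prior to each treatment during the first week (i.e., thrice-weekly), and then at weekly intervals"), modelled as after treatments 1, 2, 3, 6, 9 and 12.

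**Inputs assumed.** The fraction without response after treatment 9, S(9), is 0.20 to 0.50. This takes the background ECT response rate as the rate at treatment 9 in both arms; the article ties that rate to no treatment count and states no design response rate.

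**Step 1, algebra.** Let A(t) be the area under the curve up to treatment t. No rating falls between treatments 9 and 12, so the curve is flat there and

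A(12) − A(9) = 3 × S(9).

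This gives 3 × 0.20 = 0.6 and 3 × 0.50 = 1.5 treatments.

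**Step 2, one illustrative curve.** Take S = 0.95, 0.90, 0.85, 0.60 and 0.45 after treatments 1, 2, 3, 6 and 9.

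- A(9) = 1 + 0.95 + 0.90 + 3(0.85) + 3(0.60) = 7.20
- A(12) = 7.20 + 3(0.45) = 8.55
- Difference = 1.35 treatments, with identical curves.

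**Step 3, simulation of identical arms.** Settings: exponential time to first response (assumed), 100 per arm, 1,500 trials per setting, ketamine non-responders observed to 9. A fraction of ECT patients is followed to 12 and the rest to 9; fractions of 0.25, 0.5 and 1.0 were tried. Results for 0.5, with differences taken before rounding:

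| Response by 9 | Ketamine mean, own last time | ECT mean, own last time | Difference | Difference, common limit 9 |
|---|---|---|---|---|
| 50% | 7.06 | 8.56 | 1.50 | 0.00 |
| 60% | 6.55 | 7.76 | 1.20 | 0.01 |
| 65% | 6.30 | 7.34 | 1.04 | −0.01 |
| 70% | 6.00 | 6.90 | 0.90 | 0.00 |
| 80% | 5.32 | 5.92 | 0.60 | −0.01 |

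The difference follows 3 × S(9) and hardly changes with the fraction of ECT patients followed to 12. The standard deviation of the difference is about 0.5, so the artefact is about 0.60/0.5 = 1.2 to 1.50/0.5 = 3 standard deviations.

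A mean among responders only leans the same way: at 60% response and half of ECT followed to 12, it is 4.93 for ketamine and 5.50 for ECT.

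**Step 4, alternatives.** With a common limit of 9, the difference is within 0.01 treatments of zero in every setting. A two-sided log-rank test at 5% rejects in 4.1–5.8% of trials. That is expected: after treatment 9 only ECT patients remain at risk, so ECT responses at 12 add nothing to the test statistic.

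**The case against.** A reader might infer that the plan makes ketamine look faster by construction. The documents do not support that. The artefact arises only if each mean runs to its arm's own last time, or if only responders are averaged, and the article specifies neither. A log-rank test is the usual companion to a Kaplan-Meier comparison and is not distorted here. Nor is a truncation at 9 for one arm and 12 for the other written anywhere. The limit of 9 for ketamine follows from who receives the extra infusions, and 12 is only a maximum for ECT, since the physician may stop at 9 and ECT non-responders may also cross over after 3 weeks.

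Two further inferences also fail. One is that patients who cross over are wrongly censored: the article gives no censoring rule, and crossover after 3 weeks does not disturb the curves through treatment 9. The other is that the weekly rating interval adds to the bias: both arms are rated on an identical schedule, so it coarsens them alike.

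It is also fair to say that a restriction point and a test for an endpoint outside the primary comparison are commonly left to the full protocol or analysis plan. That would settle the matter if the article had only been silent. But it commits to a particular summary, which cannot be estimated as stated. An analysis plan would have to qualify or replace it; one that followed it literally would need a limit, and the two arms' natural limits differ.

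**Conclusion.** The point holds in a conditional form. Without a restriction, the stated mean is not estimable when a sizeable fraction does not respond. The stopping rules can give ECT up to 3 more treatments in which a first response may be observed. If each mean is taken to its own last time, identical arms differ by 3 × S(9) in ketamine's favour: about 0.6 to 1.5 treatments for S(9) of 0.20 to 0.50.

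The size rests on that assumed range and on at least some ECT non-responders reaching treatment 12. The simulation further assumes an exponential response process and a choice of 9 or 12 ECT treatments unrelated to prognosis. The primary non-inferiority comparison of response rates is not affected by this point. Speed is nevertheless named in the primary objective and compared directly, so the wording should be changed.

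**What to change.** Replace the stated mean with the restricted mean number of treatments to first response, limited to 9 treatments in both arms, and report the between-arm difference with a 95% confidence interval. Add a log-rank or discrete-time comparison through treatment 9, stratified by centre to match the randomization.

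The cost is a change of analysis wording; it uses ratings already collected and alters no treatment rule. The common limit also avoids any dependence on why a physician chose 9 or 12 ECT sessions. The downside is that first responses to ECT at treatments 10 to 12 no longer count in the speed comparison; they can be reported descriptively.

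### Speed is compared on Kaplan-Meier means with no common horizon; if any ECT non-responder goes past treatment 9, the usual means run to 9 for ketamine and 12 for ECT and favour ketamine even when response curves are identical

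*Protocol article*

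**What the plan says.** All references are to the protocol article.

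- **Endpoint (Data analyses).** "Speed of therapeutic effects is defined as the number of treatments required for participants to first meet antidepressant response criteria".
- **Analysis (Data analyses).** "A Kaplan-Meier survival analysis will be used to compare the mean number of required treatments for first response to ECT and ketamine". The comparison is confined to the randomized treatment phase. No truncation point and no test are named.
- **ECT course (Randomized treatment phase).** "For participants receiving ECT, the number of treatments (9 or 12) is determined by the treating physician". The choice is not tied to response.
- **Ketamine course (Randomized treatment phase).** "For the ketamine arm, the number of treatments is determined by participants’ antidepressant response as assessed using the MADRS". Remitters "after 9 ketamine infusions exit the randomized treatment phase and are eligible to enter the maintenance phase". For the rest, "Participants receiving ketamine who achieve an antidepressant response but not remission after 9 treatments receive an additional 3 infusions".
- **Non-responders, both arms (Randomized treatment phase).** They "after 3 weeks may crossover to receive a full course of treatment with the alternative strategy". This is permission, not an obligation.
- **Rating times (Clinical platform).** Ratings are taken before each treatment in week 1 and weekly after that.

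Speed is one of the four parts of the primary objective (Background), and the Discussion expects ketamine to act faster.

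**The concern.** A Kaplan-Meier mean is ordinarily the area under the curve up to the last observed time. It therefore depends on how long participants who have not yet responded are followed, as well as on how fast participants respond.

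Here the course rules make that length differ by arm. In the ketamine arm, everyone who receives infusions 10 to 12 has already had the event, and the only continuation stated for a non-responder at 3 weeks is crossover. The set still at risk of a first response is empty after treatment 9. In the ECT arm, a participant without response at 9 may continue and first respond by 12. The two means then cover 0 to 9 and 0 to 12 treatments.

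At stake is a false finding on a stated objective, in the direction that the Discussion expects. The cause is neither drop-out nor rating frequency, so better follow-up would not remove it.

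**Working it through.** The article gives no figure for the speed comparison, so there is none to reproduce. The check asks what the stated contrast returns when the two treatments are equally fast.

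**Inputs**
- Response range: 50 to 80%, the ECT range in the Background, taken here as response by treatment 9 and set equal in both arms.
- Ratings: after 1, 2, 3, 6, 9 and 12 treatments (Clinical platform).
- Course rules: ketamine non-responders are censored at 9; ECT non-responders continue to 12 with probability q.
- Size: 100 per arm (Data analyses).
- Assumption: a constant response probability per treatment, so S(t) = S(9)^(t/9).

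**Means to each arm's own last time**

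Ketamine, 0 to 9: 1 + S(1) + S(2) + 3·S(3) + 3·S(6).

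ECT, 0 to 12: the same sum plus 3·S(9), because no rating falls between 9 and 12 and the curve is flat there.

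The difference is therefore 3 × S(9), whatever the shape of the common curve before treatment 9.

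Worked at 50% response, S(9) = 0.50:
- Ketamine: 1 + 0.926 + 0.857 + 3(0.794) + 3(0.630) = 7.05.
- ECT: 7.05 + 3(0.50) = 8.55.

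| Response by treatment 9 | Ketamine mean | ECT mean | Spurious gap |
|---|---|---|---|
| 50% | 7.05 | 8.55 | 1.50 |
| 60% | 6.56 | 7.76 | 1.20 |
| 70% | 5.99 | 6.89 | 0.90 |
| 80% | 5.32 | 5.92 | 0.60 |

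**Dependence on q.** Simulated gaps for q of 0.25, 0.5 and 1 were 1.50 to 1.52 at 50% response, 1.19 to 1.21 at 60% and 0.88 to 0.90 at 70%. How many ECT non-responders continue hardly matters, as long as some do. At q = 0 the gap was within 0.01 of zero.

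**Consequence for a test.** Suppose the difference in these means is tested with a two-sided 5% z-test. Identical treatments then give a result in ketamine's favour in about 87%, 65%, 40% and 22% of trials at 50%, 60%, 70% and 80% response, against a nominal 2.5% in that direction.

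**Alternatives on the same simulated data (50 to 70% response)**
- Both means restricted to 9 treatments: average difference 0.00 to within simulation error, two-sided rejection about 4 to 6%.
- Log-rank test: about 4 to 6%.
- Mean among responders only: shifted the same way, by 0.2 to 1.2 treatments when q is 0.25 or more.

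Carrying the ketamine curve flat to 12 also gives no gap with weekly ratings.

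**The case against.** The strongest reply is that the article fixes less than the calculation assumes. It names no test, no limit of integration and no software convention. A log-rank test is the usual companion of a Kaplan-Meier analysis and keeps its level. A shared limit removes the gap. An analysis plan that is not shown could set either, and a journal article may leave such detail to that plan.

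Much of this stands, and it rules out three stronger readings that a reader might infer.

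- **That the protocol prescribes an analysis with a false-positive rate of 22 to 87%.** Those rates belong to a z-test on means taken to unequal limits, which the article does not name.
- **That the bias is certain.** It needs at least one ECT non-responder to continue past treatment 9. The course rules permit this but do not guarantee it, since ECT non-responders may also cross over at 3 weeks. The study-design figure was not available to settle how often it would happen.
- **That the trial's main conclusion is at risk.** The primary outcome, the margin and the sample size all concern the response rate, which this point does not touch.

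The reply does not remove the point. The article commits to comparing means, and following that literally under its own course rules can give a wrong answer. That is more than an omitted detail. A mean among responders only would not help either, because it is shifted the same way.

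**Conclusion.** The point holds conditionally and is of moderate severity. Two conditions are needed: some ECT non-responder continues past treatment 9, and each mean is taken to its own arm's last observed time. Under both, the stated comparison adds 3 × S(9) treatments to the ECT mean when nothing differs, which is 0.6 to 1.5 treatments over 80% to 50% response by treatment 9.

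The gap formula assumes equal response curves, no rating between treatments 9 and 12, and no drop-out. The tabulated means and the test rates also assume a constant per-treatment response probability. If either condition fails, the gap is zero.

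**What to change.** In the analysis wording for speed, replace the comparison of Kaplan-Meier means with the **restricted mean number of treatments to first response, with one common horizon of 9 treatments in both arms**. Give the difference with its confidence interval and test that difference. A log-rank test is an acceptable companion. Report ECT first responses at treatments 10 to 12 separately, and fix the horizon before outcome data are examined by arm.

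The cost is a change of wording only: no treatment, visit or sample-size change. The small downside is that late ECT first responses leave the speed measure. They still count in the response rate.
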